#### Secondary analyses

With a public health intervention, such as Newhints, it is impossible to ensure every eligible recipient receives the intervention in exactly the way it was intended. Thus it is likely that only a proportion of pregnant women residing in intervention zones will receive all five home visits at the timing intended; others may not have received any, or fewer visits, or visits later than intended, in particular the first post-natal visit may not have taken place within 24 hours as intended. Secondary analyses will therefore also be carried out to examine whether the impact of the intervention varies according to the number and timing of home visits each woman has received, and the average quality of the intervention delivered in the zone, as assessed by the process indicators measured on a sub-sample of women (see below). This will be explored both using individual quality indicators and by dividing intervention zones into quintiles, based on a quality index derived using principle component analysis [17].

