### Primary objectives

1. To link with District Health Management Teams (DHMTs) to develop a feasible and sustainable intervention to improve newborn care practices and careseeking through training the current network of community based surveillance volunteers (CBSVs) to identify pregnant women in the community and to conduct two home visits during pregnancy and three in the first week of life of the neonate.

2. To evaluate the impact of these home visits on all cause neonatal mortality.

3. To evaluate their impact on newborn care practices.

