### Overview of Trial Design

The Newhints intervention is being evaluated through a cluster randomised controlled trial design. The clusters are Newhints zones which correspond to supervisory units of about 8-12 CBSVs. There are 98 Newhints zones in total; 49 zones randomised for implementation of the Newhints intervention, with the other 49 zones acting as controls. The trial planning started in October 2006. The Newhints intervention was developed and fully implemented in the intervention zones by the end of 2008. Impact data on neonatal mortality and newborn care practices is being collected through ongoing surveillance of all women of child-bearing age and their infants in the trial area, and will be based on approximately 15,000 babies born from 1 January 2009. Detailed process, cost and cost-effectiveness evaluations are also being carried out. Data collection is expected to be completed in April 2010 and analysis will take place throughout 2010.

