	- Teach newborn danger signs & encourage prompt care-seeking

**Day 7**	- Assess baby for danger signs & refer sick babies
	- Reinforce EBF, thermal care, prompt care-seeking
	- Encourage bed net use, immunisations

**Other visits**	- Follow-up visits within 24 hours for referred babies
	- Visit at 14 days for LBW babies

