### Sample size

The sample size was determined by the primary outcome, all cause neonatal mortality, using the baseline neonatal mortality rate (NMR) of 31 per 1000 live births and the intraclass correlation coefficient (ICC) of 0.0007256, where the ICC[14] is defined as the ratio of the between zone variation to the total variation. This suggests that a total sample size of 15,200 livebirths would have 80% power to detect a 25% reduction in NMR at the 5% significance level, 93% power to detect a 30% reduction and 60% power to detect a 20% reduction. This sample size should be achieved by the number of livebirths that take place in a year in the trial area. The evaluation will be based on data collected for all babies born from 1 January 2009; this is 1 month after the intervention was fully implemented, and 6 months after CBSVs started assessing babies in July 2008 as well as counselling about newborn care practices.

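### The secondary analysis of impact by home visits received is open to survivor bias when the outcome is neonatal death, because three of the five visits fall inside the outcome window

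*Protocol article*

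**What the plan says.** The intervention consists of "two home visits during pregnancy and three in the first week of life of the neonate" (Primary objectives). Table 1 places the postnatal visits on the day of birth, day 3 and day 7. The Background defines the neonatal period as the first 28 days, and Impact evaluation names all-cause neonatal mortality and key care practices as the primary outcomes.

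The primary analysis of each outcome is by intention to treat, according to the woman's zone of residence (Intention-to-treat analyses). The Secondary analyses section then expects incomplete delivery and plans to "examine whether the impact of the intervention varies according to the number and timing of home visits each woman has received", and also by the average quality of delivery in the zone. It explains missed or late visits only by imperfect delivery. It does not mention that a visit may be missed because the baby has died. It names no landmark, time-varying exposure or restriction to pregnancy visits.

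**The concern.** A visit due on day 3 or day 7 can be made only to a baby still alive. If visits received are the exposure and any death to day 28 is the outcome, the early deaths collect in the groups with few visits, and the fully visited group is by construction made up of babies who survived to day 7. More visits will go with fewer deaths even if visits have no effect. The remedies the article names do not remove this. Its covariates are maternal characteristics and zone baselines, and logistic regression on a 28-day outcome carries no information on who was alive when a visit fell due.

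The practical risk arises if the intention-to-treat result is null or small. A steep gradient by visits received could then be read as showing that the programme works and only coverage was at fault. The article intends its findings to inform scaling up and policy.

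**Working it through.** **The plan's own benchmark.** Inputs from Sample size and Overview of Trial Design: "baseline neonatal mortality rate (NMR) of 31 per 1000 live births", "intraclass correlation coefficient (ICC) of 0.0007256", 98 zones split 49:49, and 15,200 livebirths.

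- Mean zone size: 15,200/98 = 155.1. Design effect: 1 + 154.1 × 0.0007256 = 1.112. Effective number per arm: 7,600/1.112 ≈ 6,836.
- For a 25% reduction: 0.031 versus 0.02325, difference 0.00775. SE = √[(0.031×0.969 + 0.02325×0.97675)/6,836] = 0.00278. Power = Φ(0.00775/0.00278 − 1.96) = Φ(0.83) ≈ 79.7%, two-sided 5%.
- The same steps give 92.4% for a 30% reduction and 59.5% for 20%. The stated values are 80%, 93% and 60%, so they reproduce. The design effect to compare against is a relative risk (RR) of 0.75.

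**Null model for visits.** Visits have no effect. Every baby has neonatal risk p = 0.031. Each postnatal visit is made with probability c, independently of risk, if the baby is alive when it is due. The day-of-birth visit is made with probability c to all babies, which understates the problem. Let a be the share of neonatal deaths after the day-7 visit. The article gives neither a nor c, so both are assumptions.

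- Risk with all three visits = pa/(1 − p + pa). The factor c³ cancels, so this does not depend on coverage.
- Risk with fewer = p(1 − c³a)/[1 − c³(1 − p + pa)].

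**Main range, 60-75% of deaths in week 1 (a = 0.40 to 0.25).**

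- a = 0.40: 0.0124/0.9814 = 12.6 per 1000, which is 59% below 31.
- a = 0.25: 0.00775/0.97675 = 7.9 per 1000, which is 74% below 31.

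**Wider range, all three visits versus fewer.**

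| Deaths before day 3 | Day 3 to 7 | After day 7 | c | All three, per 1000 | Fewer, per 1000 | RR |
|---|---|---|---|---|---|---|
| 30% | 10% | 60% | 0.4 | 18.8 | 31.8 | 0.59 |
| 50% | 15% | 35% | 0.6 | 11.1 | 36.3 | 0.30 |
| 75% | 10% | 15% | 0.8 | 4.8 | 57.1 | 0.08 |

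The true RR is 1.00 in every row.

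**Break-even.** The fully visited group falls 25% below 31 per 1000 when pa/(0.969 + pa) = 0.02325. That gives pa = 0.02253/0.97675 = 0.02307 and a = 0.744. So the artefact exceeds the 25% design effect whenever more than about 26% of neonatal deaths precede the day-7 visit.

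**Effect and price of a landmark.** Among babies alive at day 7, the null model gives the same later risk whatever visits were received, so the expected RR is 1.00. The price is events. Half of 15,200 births at 31 per 1000 gives 7,600 × 0.031 ≈ 236 deaths in the intervention arm.

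- 24-hour landmark, if 25-35% of deaths fall on the first day: 153-177 deaths remain.
- Day-7 landmark, if 60-75% fall in week 1: 59-94 remain. Over the wider range (a = 0.15 to 0.60): 35-141.
- If timing exists only in the PROCESS subsample of 200-300 women a month, taken over 12 months: 2,400-3,600 women and, at one birth each, 74-112 deaths in all. About 37-56 would be in intervention zones if half the sample is there (an assumption).

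**The case against.** The article is condensed. It names no outcome, comparator or model for this analysis, and impact also covers care practices, for which visit counts do not raise this survivor problem. A full analysis plan could contain a landmark. That limits the point but does not dispose of it: the article states the exposure as visits actually received, includes mortality within impact, and gives no safeguard. This is a stated rule that misleads for one outcome, not an omitted detail.

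Some stronger readings are tempting but unsupported:

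- A reader might infer that the count also rises with risk, because sick and low-birth-weight babies get extra visits. Table 1 lists "Follow-up visits within 24 hours for referred babies" and the 14-day visit separately under other visits, and both the Secondary analyses section and the process indicators speak of five visits. Nothing says the extras are counted.
- A reader might infer that the trial's main result is compromised. The primary analysis is by zone of residence and does not use visits received.
- A reader might extend the bias to the zone-quality quintiles. These rest on zone averages, not on a baby's own visits, and are largely free of it.
- A reader might think the remedy needs no further data and costs few events. Impact evaluation says only that the BIRTH form records contact with volunteers. Detailed visit information is described for the PROCESS subsample. The loss of events is substantial, as shown above.

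**Conclusion.** The point holds for one analysis: individual postnatal visits received, with neonatal mortality as the outcome. The direction of the bias follows from the article's own visit schedule and outcome window. Its size rests on assumed age at death and, for the contrast with less-visited babies, on assumed coverage. With 60-75% of deaths in week 1, the fully visited group shows about 8-13 per 1000 when visits do nothing. Across the wider range the spurious RR for all three visits versus fewer is 0.08 to 0.59, and even the mildest value is further from 1 than the design effect of 0.75. The intention-to-treat analysis, sample size and care-practice outcomes stand. Severity: should be fixed, because the analysis is secondary but its mortality result would mislead.

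**What to change.** For mortality, amend the Secondary analyses section as follows.

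- Use the number of pregnancy visits (0, 1 or 2) as the individual exposure for all births. These precede the outcome.
- Analyse postnatal visits only by landmark or as a time-varying exposure. Examples are a first visit within 24 hours against death after 24 hours among babies alive at 24 hours, and visits by day 7 against death after day 7 among babies alive then. If control babies are the comparator, apply the same survival condition to them.
- Do this wherever visit timing is recorded: the BIRTH form if it holds timing, otherwise the PROCESS subsample.
- State that only the scheduled visits are counted.
- Label all these comparisons as non-randomised. That applies to pregnancy visits too, since a preterm birth can pre-empt the third-trimester visit. Report the postnatal-visit results as exploratory.

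The cost is wording, some programming and a check of which form holds visit timing. The real price is precision: about 25-35% of deaths are lost at 24 hours and 60-75% at day 7 under the stated assumptions, with far fewer events if only the PROCESS subsample has timing. Visit counts may still be used for care-practice outcomes.

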### Randomisation

Meetings were held in each district in November 2007 to introduce the Newhints trial to all CBSVs, to explain the proposed randomization process and to obtain their cooperation and support for this; 686 CBSVs (91%) attended. Forty-nine zones were then selected at random for implementation of the Newhints intervention, with the other 49 zones acting as control. This was carried out by an independent epidemiologist using restricted stratified randomisation to ensure balanced numbers of intervention and control zones in each of 10 strata. These were the four large towns (Kintampo, Nkoranza, Techiman and Wenchi) and the six districts (Kintampo North, Kintampo South, Nkoranza, Tain, Techiman and Wenchi) minus these towns; note this took place before Nkoranza was divided into two districts, Nkoranza North and Nkoranza South. Restricted randomisation used available surveillance data to ensure that intervention and control arms were also balanced with respect to the following criteria: absolute differences of less than 2/1000 live births for neonatal mortality rates, less than 2.5% for the percentage of deliveries in a health facility, and less than 2.5% for the percentage of deliveries in a private hospital, in each of 2004, 2005 and 2006. An additional selection criterion was to ensure that the 4 pilot zones (which had been chosen at random) were allocated to the intervention group.

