#### Participant flow & comparability of treatment arms

A flow diagram will be completed showing the number of zones, pregnancies, livebirths, neonatal deaths and loss to follow-up in the intervention and control arms, together with a map showing the locations of the intervention and control zones. Intervention and control zones will be compared with respect to the following variables: neonatal mortality rate, the percentage of skilled attendants at delivery and percentage of deliveries occurring in health facilities in 2007 (baseline); level of education of mothers, their ethnic group of origin, marital status and parity, and occupation (used as proxy indicator for the level of income), since these are known either to be related to the neonatal mortality rate or to effect peoples' knowledge, attitudes and practices on neonatal care. No statistical significance tests will be carried out on these comparisons [14,16]. However, analyses will be carried out both including and excluding these potential *a priori *confounders.

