In-depth interviews and focus group discussions will also be carried out with a range of respondents (recently-delivered women, their families, CBSVs, TBAs, health facility staff) to explore all aspects of the intervention delivery and response to recommendations. Special sub-studies will focus on the provision of special care for low birthweight babies, and the assessment and referral of sick and very low birthweight babies.

Summary statistics and graphs showing trends over time will be compiled for all the process indicators, and determinants of quality of intervention delivery explored. The transcripts from in-depth interviews and focus group discussions will be formally analyzed using Nvivo software. Key analytical categories will be identified and the interviews systematically indexed into these categories and interpreted in order to make recommendations concerning intervention implementation, identify factors contributing to success, document barriers encountered and strategies adopted to tackle them, and identify issues important for scaling up.

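### The quality-quintile analysis compares non-randomised groups of intervention zones, so a gradient in 2009 outcomes can reflect risk that preceded Newhints rather than variation in impact

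*Protocol article*

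**What the plan says.** The Secondary analyses section sets out to "examine whether the impact of the intervention varies according to the number and timing of home visits each woman has received", and likewise according to the average quality of delivery in the zone, "as assessed by the process indicators measured on a sub-sample of women". Individual quality indicators will be used, and also "dividing intervention zones into quintiles, based on a quality index derived using principle component analysis". No comparator for the quintiles is named, and neither a model nor a test is given.

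On the outcome period, the Sample size section says: "The evaluation will be based on data collected for all babies born from 1 January 2009".

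Two other parts of the protocol bear on the point.
- **Adjustment.** Intention-to-treat analyses says that all analyses will be run with and without adjustment for potential confounders. The list under Participant flow & comparability of treatment arms has the 2007 neonatal mortality rate (NMR), skilled attendance and facility delivery, and maternal education, ethnic group, marital status, parity and occupation.
- **Earlier data.** Under Randomisation, "Restricted randomisation used available surveillance data to ensure that intervention and control arms were also balanced", with criteria for NMR and place of delivery in each of 2004, 2005 and 2006. That balance is between arms. Nothing balances the later quality quintiles.

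**The concern.** The question is about impact, meaning what Newhints changed. The grouping exists only in the intervention arm and is fixed by what happened after randomisation. A contrast between well-served and poorly served zones is then a contrast of outcome levels, and it equals a contrast of impact only if the groups would have had the same outcomes without Newhints. The zone random effect does not secure this, because the model takes it to be independent of the quality index.

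A link between quality and prior risk is plausible but not shown. Mapping zones describes zones that range from parts of large towns to geographically separated communities. Process evaluation and intervention monitoring plans to have "determinants of quality of intervention delivery explored", so quality is expected to vary for reasons worth studying.

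If hard-to-reach zones had both weaker delivery and higher mortality, the analysis could show a dose-response where the effect was equal everywhere or absent. The opposite pattern could hide a real one.

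**Working it through.** **Inputs from the protocol (Sample size; Overview of Trial Design).** NMR p = 0.031; ICC = 0.0007256; 15,200 live births; 98 zones, 49 per arm. The correlation r between higher quality and lower prior zone risk is an assumption, taken from 0 to 0.7.

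**1. The protocol's own figures.** Births per zone m = 15,200/98 = 155.1. Design effect = 1 + 154.1 × 0.0007256 = 1.112. Power for reductions of 25%, 30% and 20% comes to 79.7%, 92.4% and 59.5%, against 80%, 93% and 60% stated. The required total is 13,792 × 1.112 ≈ 15,334, against 15,200. The inputs are therefore being read as intended.

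**2. Why a shared control group does not help.** Let R_q be the rate quintile q would have had in 2009 without Newhints, E_q the true rate ratio there, and C the control rate. Each quintile against control gives R_q·E_q/C. Top against bottom gives (R_5/R_1) × (E_5/E_1). C cancels, and the result equals E_5/E_1 only if R_5 = R_1.

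**3. How much zones differ beforehand.** Between-zone SD = √(0.0007256 × 0.031 × 0.969) = 0.00467, or 4.67 per 1000, so k = 0.00467/0.031 = 0.151. True zone rates then run from about 22 to 40 per 1000 (31 ± 1.96 × 4.67).

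**4. What the 2007 zone NMR can adjust for.** One zone-year has about 155 × 0.031 = 4.8 deaths. Sampling variance ≈ 0.031 × 0.969/155.1 = 0.000194; between-zone variance = 0.00467² = 0.0000218. Reliability = 0.0000218/(0.0000218 + 0.000194) = 0.10. With four years of data it is 0.31.

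**5. Simulation for mortality.** 49 intervention zones of 155 births, 20,000 runs, the same effect in every zone, and zone risk fully persistent from the pre-trial years to 2009. A zone-level trend test over quintiles at 5% stands in for the unspecified model. With no effect in any zone:

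| Assumed r | Apparent rate ratio, top v bottom | Rejection, unadjusted | Rejection, adjusted for 2007 NMR | Rejection, change from pre-trial |
|---|---|---|---|---|
| 0 | 1.00 | 5% | 5% | 5% |
| 0.3 | 0.88 | 10% | 9% | 5% |
| 0.5 | 0.81 | 18% | 15% | 5% |
| 0.7 | 0.74 | 30% | 26% | 5% |

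With a uniform 25% reduction, unadjusted rejection is 5%, 8-9%, 15% and 23-24% at the same values of r. At r = 0.5 adjustment brings it to 13%.

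At r = 0.5 with no effect, adjusting for 2007 NMR moves the false top-to-bottom gradient from -6.2 to -5.7 per 1000 (5.7/6.2 = 92% remains). Four baseline years as a covariate leave -4.6 (74%).

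**6. Information available.** Each quintile holds about 7,600/5 = 1,520 births and 1,520 × 0.031 = 47 deaths. Power for a true 25% difference between top and bottom is about 24%. Where false rejection may reach 15% or more, a significant trend taken alone says little.

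**The case against.** **The protocol names no comparator, model or test.** This is right. The trend test above is a stand-in, and an unseen analysis plan may say more. But the grouping itself is stated, and step 2 holds for either comparator.

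**The planned adjustment is fuller than the one simulated.** This is the strongest point. The list includes 2007 facility delivery, which a zone-year measures far better than mortality. At an assumed ICC of 0.01 to 0.05, reliability is 155 × 0.01/(1 + 154 × 0.01) = 0.61 to 155 × 0.05/(1 + 154 × 0.05) = 0.89. If all the confounding ran through access to facilities, adjusting for facility delivery and NMR together (assumed facility ICC 0.03) brought rejection at r = 0.3, 0.5 and 0.7 from 8%, 14% and 24% to 5%, 5% and 6%. So the adjusted column above is not the residual bias of the planned analysis. How much of the confounding runs through the listed covariates cannot be known from the documents.

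**Both the bias and the remedy depend on persistence of zone risk.** This also stands. With a correlation of 0.7 between pre-trial and 2009 zone risk, unadjusted rejection falls to about 7%, 10% and 13% at r = 0.3, 0.5 and 0.7 under a uniform effect. With a correlation of 0.3, the change contrast itself rejects 10-15% of the time at r = 0.5 to 0.7. Its clean 5% above follows from assuming full persistence.

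**Stronger readings that the documents do not support.** A reader might infer that the plan will report a false dose-response; it can, but r is not documented. A reader might infer that the analysis is purely a comparison of levels; that overlooks the planned adjusted version. A reader might also infer that a false gradient would pass straight into scale-up recommendations; the protocol ties those to the interviews and focus groups.

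**Conclusion.** The point holds in a limited form. The quintiles are not randomised, so a gradient across them in the evaluation births is not by itself evidence that impact varied. Adjustment for 2007 zone NMR removes only about a tenth of the mortality bias. The rest of the covariate list may remove more, by an amount that cannot be determined here.

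The false-positive rate of a 5% mortality trend test runs from 5% to about 25-30% as r goes from 0 to 0.7. This assumes fully persistent zone risk and an equal effect in every zone, and it is smaller if risk persists less. The analysis is secondary and exploratory, and the primary comparison by zone of residence is unaffected. The change is worth making because the trial already holds the data for it.

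**What to change.** In Secondary analyses:

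1. Report neonatal mortality and facility delivery for 2004-2007 by quality quintile as a placebo check. A gradient there cannot be due to Newhints home visits, since volunteer training began in February 2008. For mortality, a flat result is only weak reassurance, because four years of zone data have a reliability of about 0.31.
2. Keep the adjusted 2009 comparison. Beside it, fit a random-effects logistic model to the 2004-2007 and evaluation births with quintile, period and quintile × period, using the control zones' change as the reference for secular trend. Claim variation in impact only if the gradient is also seen in this contrast. The contrast should be added and not substituted, because it fails in its own way when zone risk does not persist.
3. For care practices without pre-trial data, report the gradient as an association and not as variation in impact.

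**Cost.** Some wording and one extra model on surveillance data already in use. Four pre-trial years add about one quarter to the sampling variance, so that part of the standard error grows by about √1.25 - 1 = 12%. The contrast assumes parallel trends across quintiles and persistent zone risk, and the plan should say so.
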